### Statistical analyses

All analyses will be performed on an intention-to-treat basis. Missing data on the HADS and CWS will be imputed using half-scale mean substitution methods. Data of participants who complete and return their first follow-up questionnaire after their final counseling session will be omitted from the analysis, because knowing the DNA-test result might influence questionnaire responses. Between rater agreement on the audiotaped sessions will be assessed by calculating the percentage of absolute agreement. Effect sizes will be calculated using standard statistical approaches.

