**Methods:**

This multicenter, randomized controlled trial will include 264 individuals undergoing cancer genetic counseling in two family cancer clinics in the Netherlands. Participants will be randomized to either: (1) an intervention group that completes the PAHC questionnaire, the results of which are made available to the genetic counselor prior to the counseling session; or (2) a control group that completes the PAHC questionnaire, but without feedback being given to the genetic counselor. The genetic counseling sessions will be audiotaped for content analysis. Additionally, study participants will be asked to complete questionnaires at baseline, three weeks after the initial counseling session, and four months after a telephone follow-up counseling session. The genetic counselors will be asked to complete questionnaires at the start of and at completion of the study, as well as a checklist directly after each counseling session. The questionnaires/checklists of the study include items on communication during genetic counseling, counselor awareness of their clients’ psychosocial problems, the (perceived) need for professional psychosocial support, cancer worries, general distress, specific psychosocial problems, satisfaction with care received, and experience using the PAHC questionnaire.

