### Recruitment and randomization

All eligible counselees will receive an invitation letter from the family cancer clinic, an informed consent form, a baseline questionnaire, and a return envelope three weeks before their first counseling session. Upon returning the completed informed consent form and the baseline questionnaire, we will randomize the participants on a 1:1 basis to either the intervention group or the control group. The minimization method will be used to balance the intervention and control group for each counselor in terms of gender and the cancer syndrome for which genetic counseling is requested
[28]. Neither the counselees nor the counselors will be (or can be) blinded to group assigment.

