### Timing and content of study measures

Counselees will be asked to complete questionnaires at: (1) baseline, prior to randomization; (2) approximately 4 weeks following the first genetic counseling session, before the final counseling session takes place; and (3) approximately 4 months after the telephone-based counseling session.

The counselors will be asked to complete a baseline questionnaire at the start of the study, a checklist at the end of each counseling session, and a final questionnaire at the end of the study. Both the in-person and the telephone-based genetic counseling sessions will be audiotaped by two independent raters ([name]) for purposes of content analysis (see below). Inter-rater reliability will be assessed by double coding 10% of the audiotaped sessions, equally divided between the intervention group and control group sessions.

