### Sample size and power calculations

We have based the sample size estimates on expected differences between the intervention group and the control group in communication between the genetic counselors and counselees about psychosocial issues. Overall power calculations for estimating sample size requirements were based on the following criteria for defining a substantively meaningful statistical association: (1) power of 0.80, (2) alpha of 0.05, and an (3) effect size “d” of 0.4. With these criteria, 99 cases per study arm are needed, resulting in a total sample size of 198 cases.

We anticipate that approximately 25% of the counselees will not have more than one counseling session and thus will not have a DNA-test disclosure session. Therefore, in order to have sufficient power in the second phase of the trial, we will include 264 participants at the start of the trial.

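### The omission of late T1 returners conflicts with the intention-to-treat statement and is worded more broadly than its reason, which concerns questionnaire responses only

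*Protocol article*

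**What the plan says.** Three statements in the protocol article bear on this point.

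- **Analysis population** (Statistical analyses): "All analyses will be performed on an intention-to-treat basis".
- **Exclusion** (same paragraph, two sentences later): "Data of participants who complete and return their first follow-up questionnaire after their final counseling session will be omitted from the analysis". The reason given is that knowledge of the DNA-test result could affect how people answer questionnaires. The text does not say which analysis is meant, or that only T1 scores are affected.
- **Sample size** (Sample size and power calculations): for an "effect size “d” of 0.4", "99 cases per study arm are needed, resulting in a total sample size of 198 cases". About a quarter of counselees are expected to have no disclosure session, so "in order to have sufficient power in the second phase of the trial, we will include 264 participants at the start of the trial".

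The sources of the primary outcomes are set out under Primary outcome measures. Discussion of problems and referrals are coded from audiotapes. Awareness comes from a checklist that the counselor fills in straight after each session, compared with the PAHC questionnaire completed before it. Only actual use of psychosocial services is self-reported by the counselee.

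**The concern.** An intention-to-treat analysis keeps randomised participants in the comparison whatever they do afterwards. This rule removes some of them for returning a form late. Counselees and counselors know the allocation (Recruitment and randomization), and so do the audiotape raters (Methodological issues). Speed of return could plausibly depend on arm, on distress, or on how quickly DNA testing was completed. If it does, those who remain are no longer protected by randomisation.

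The rule is also wider than its reason. Influence of the DNA result on questionnaire answers is an argument about T1 scores. It does not apply to a session 1 recording or checklist, which exist before disclosure. Nor does it justify dropping phase II or T2 data, which come after disclosure for everyone who reaches that stage. Left as it stands, the wording allows the scope to be chosen after the data have been seen.

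**Working it through.** **1. Reproduce the plan's figures.** Inputs from Sample size and power calculations: alpha 0.05 (two-sided assumed, because it reproduces 99; one-sided would give 78), power 0.80, d = 0.4, with 1:1 allocation from Recruitment and randomization.

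- n per arm = 2(1.960 + 0.842)² / 0.4² = 98.1, rounded up to 99; total 198.
- Enrolment = 198 / (1 − 0.25) = 264, and 264 × 0.75 = 198.
- Power with 99 per arm: 80.0% (t-test) or 80.4% (normal approximation).
- Power with 132 per arm (phase I): 89.9% or 90.1%.

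The stated figures hold. The 25% allowance is used up by those with no disclosure session, so at that rate phase II is left with exactly 198.

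**2. Set the reason for the rule against each data source.**

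| Data | Obtained | Could late T1 return make it invalid? |
|---|---|---|
| Session 1 audiotape (discussion, referral) | Before disclosure | No |
| Session 1 checklist and PAHC questionnaire (awareness) | Before disclosure | No |
| T1 HADS, CWS, evaluation | Before or after disclosure, by return date | Yes, on the stated reason |
| Phase II audiotape and checklist | After disclosure for all | No |
| T2 questionnaire | After disclosure for all | No |

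Only the third row fits the reason. Self-reported service use could also be affected if it is collected at T1; the article does not say at which questionnaire it is asked.

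**3. Literal reading: effect on phase II power.** Only someone with a final session can return T1 after it, so every omission comes from the 198. Let f be the share of the 198 who return late. The article gives no value, so f is assumed, with an equal split between arms. n per arm = 198(1 − f)/2, rounded to a whole number.

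| f (assumed) | n per arm | Power at d = 0.4 (t-test) | d detectable with 80% power |
|---|---|---|---|
| 0 | 99 | 80.0% | 0.40 |
| 5% | 94 | 77.9% | 0.41 |
| 10% | 89 | 75.6% | 0.42 |
| 20% | 79 | 70.5% | 0.45 |

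The normal approximation gives 78.3%, 76.1% and 71.1% for the last three rows (unrounded n). Phase I stays well above 80%: at f = 10%, n per arm is (264 − 19.8)/2 = 122.1 and power is 87.8%.

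**4. Narrow reading.** If only T1 questionnaire data are omitted, phase II keeps 99 per arm and 80% power for the audiotape outcome on which the sample size rests. The T1 comparisons of HADS, CWS and evaluation still exclude people by return time. There may be a knock-on effect at T2. Secondary research hypotheses specifies covariance analysis with the previous score as covariate. If that means T1 for the T2 comparison, an omitted T1 score removes the participant from T2 as well. Half-scale mean substitution fills gaps from the answered part of a scale, so it cannot replace a whole omitted form.

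**The case against.** The best defence is that the sentence carries its own limit. Its reason mentions questionnaire responses, and the sentence before it concerns HADS and CWS. The natural reading is then that late T1 questionnaires are left out of the T1 questionnaire analysis. The fact that the reason makes no sense for recordings or checklists supports that reading. On it, no audiotape or checklist outcome is lost and phase II power is untouched. This stands, and it is why the literal reading cannot be treated as certain. It does not settle the matter: the words used are data of participants and the analysis, without limit, and even the narrow reading departs from intention to treat for the T1 outcomes.

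A reader might infer that the rule takes phase II below 80% power. The documents do not support that as a fact. It needs both the literal reading and a late-return rate that the article does not give. T1 is scheduled before the final session, so the rate may be low; up to about 5% the loss is roughly 2 points. The 25% is also approximate: if 20% had no second session, 264 × 0.80 = 211 would remain, and a 5% loss would still leave about 200.

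A reader might also link the rule to the conflicting T1 dates: the Abstract has "three weeks after the initial counseling session", while Timing and content of study measures has "approximately 4 weeks following the first genetic counseling session", as does Table 1 in substance. The planned date may affect how many people are late, but lateness itself is defined by the final session. The conflict is a separate, minor inconsistency.

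Covariance analysis for HADS and CWS is a valid method, and replacing it is not required to correct this sentence.

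**Conclusion.** The point holds as a conflict between the exclusion and the intention-to-treat statement, together with an exclusion whose scope exceeds its reason. It is wrong as written under either reading. The literal reading discards valid primary-outcome data, and the narrow one selects on post-randomisation behaviour for the T1 questionnaire outcomes. The direction and size of any bias cannot be computed, because the documents give neither the late-return rate nor its relation to arm or distress.

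The power figures in the table are conditional on the literal reading, the assumed rates, an equal split between arms, and exactly 25% having no disclosure session. They show what the wording could cost and are not a forecast.

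**What to change.** Replace the exclusion sentence with:

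> T1 questionnaire scores (HADS, CWS, evaluation) returned after the final session are set to missing in the primary T1 analysis; the participant stays in all other analyses (session 1 audiotape, counselor awareness, referral, phase II, T2).

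In addition:

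- Report the number of late returns by arm.
- Add a sensitivity analysis that includes the late T1 scores.
- For T2 HADS and CWS, name the baseline score as covariate, or use a repeated-measures model, so that a missing T1 score does not remove the participant.
- If service use is asked at T1, say how late reports of it are handled.
- Separately, reconcile the three-week and four-week T1 timing.

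The cost is a change of wording, one short table and one sensitivity analysis. No extra participants are needed. Phase II keeps its planned 198 as far as this rule is concerned, so the power statement need not change on its account.

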#### Non-participant analysis

Based on experience with other studies, we anticipate that approximately 40% of eligible participants will decline to participate in the study. The non-participants will be compared with participants on available sociodemographic and clinical data using appropriate statistics (e.g. Student’s t-test, or non-parametric test).

#### Comparability of intervention and control group

The comparability of the intervention and control groups at baseline will first be evaluated in terms of sociodemographic and clinical characteristics. Student’s t-test or appropriate non-parametric tests will be used. If, despite the stratified randomization procedures, the groups are found to be statistically different on one or more baseline characteristics, these variables will be adjusted for in subsequent analyses.

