#### Main research hypotheses

We will evaluate group differences in the number of psychosocial issues discussed during the genetic counseling sessions using analysis of (co)variance. We will assess counselors’ awareness of their counselees’ psychosocial problems by calculating the agreement between counselees’ and counselors’ on their ratings, per domain, of the psychosocial problems experienced by the counselees. We will calculate an Intraclass Correlation Coefficient (ICC2.1.A
[34]) per domain for both the intervention and control group. Group differences will be assessed by treating the ICC’s as Pearson correlation coefficients and using Fisher’s r-to-z transformation to test for statistical differences per domain. Analysis of (co)variance will also be used to evaluate group differences in referral to additional information sources and/or referral to psychosocial care services, and the actual use of such services.

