#### Secondary research hypotheses

We will employ analysis of (co)variance to evaluate group differences in the frequency of with which the genetic counselor initiated the discussion of psychosocial issues. Analysis of (co)variance will also be used to evaluate group differences in the amount of counseling time spent discussing psychosocial issues, and the total length of the counseling session. To evaluate group differences in cancer worries and general distress, we will use analysis of covariance, with the previous scores on these questionnaires as covariate. Logistic regression analysis will be used to evaluate differences between groups in the prevalence of cancer genetics-specific problems. Group differences in satisfaction with the genetic counseling process will be examined with Student’s t-tests and chi square tests, where appropriate. Intervention group and counselor satisfaction with the intervention will be reported descriptively.

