### Methodological issues

A major strength of the study is its use of a randomized design that will ensure high levels of internal validity. The relatively large sample size, the multicenter approach, and the heterogeneity of the study sample will increase the external validity and generalizability of the findings.

Several possible limitations of the study should also be noted. First, due to the nature of the intervention, it is not possible to blind the genetic counselors, nor the counselees, nor the raters of the audiotapes to group allocation. This carries with it the risk of contamination, particularly on the part of the counselors. That is, any given genetic counselor will be seeing both counselees assigned to the intervention group and the control group. Thus, it is conceivable that the counselors’ experience with the intervention (i.e., receiving personalized feedback regarding the counselees’ self-reported psychosocial problems) will also affect the way they interact with counselees in the conrol group. We would note, however, that any such carry over effect will have a conservative effect on the study (i.e., that, if anything, it will make it more difficult to observe significant group differences on the primary study outcomes). A second possible limitation of the study will depend on the observed prevalence of psychosocial problems among counselees. If the prevalence is low, then it will be more difficult to detect group differences in the various study outcomes. Finally, due to funding limits, the follow-up period for the second phase of the trial is relatively short (only 4 months).

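### Covariates are chosen by baseline significance tests, a rule that picks chance imbalances and in effect keeps out the minimization factors, so model standard errors are too wide

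*Protocol article*

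**What the plan says.** Allocation (*Recruitment and randomization*) is 1:1 and uses minimization: "The minimization method will be used to balance the intervention and control group for each counselor in terms of gender and the cancer syndrome" (the syndrome that prompted the request).

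The covariate rule (*Comparability of intervention and control group*) compares the arms at baseline on sociodemographic and clinical characteristics. For this, "Student’s t-test or appropriate non-parametric tests will be used". If, despite the balancing procedure, "the groups are found to be statistically different on one or more baseline characteristics, these variables will be adjusted for in subsequent analyses".

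The models name no allocation factor. For the first primary outcome (*Main research hypotheses*): "We will evaluate group differences in the number of psychosocial issues discussed during the genetic counseling sessions using analysis of (co)variance". The same technique serves referral and service use. Under *Secondary research hypotheses* it also serves counselor initiation, time on psychosocial issues and session length. For problem prevalence, "Logistic regression analysis will be used to evaluate differences between groups in the prevalence of cancer genetics-specific problems". The one prespecified covariate belongs to the secondary outcomes of cancer worries and distress, where "we will use analysis of covariance, with the previous scores on these questionnaires as covariate".

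*Methodological issues* states that "any given genetic counselor will be seeing both counselees assigned to the intervention group and the control group".

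**The concern.** There are two linked faults.

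First, the selector is wrong. With randomized arms, a significant baseline difference is a chance event. It says nothing about whether the variable predicts the outcome, and predicting the outcome is what makes adjustment worthwhile. A rule driven by p-values also means that nobody can write down the primary model before seeing the data.

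Second, the rule works against the design. Minimization holds gender and cancer syndrome level between arms, so a test will seldom flag them. Counselor is not a counselee characteristic and is not among the variables to be tested. Yet issues raised, referrals and session length are partly things the counselor does, and each counselor contributes sessions to both arms. A model that ignores a balanced prognostic factor leaves its variance in the residual, although balance has already removed that variance from the treatment comparison. The reported standard error is then larger than the real one. At stake are the level of the tests, some power, and the reading of the one hypothesis that is supported by a non-significant result.

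**Working it through.** **1. The plan's own figure.** Inputs from *Sample size and power calculations*: power 0.80, alpha 0.05, d = 0.4, 25% without a second session. Sidedness is not stated; two-sided reproduces the figure.

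- n per arm = 2(1.960 + 0.842)²/0.4² = 98.1, rounded up to 99; total 198.
- 198/0.75 = 264, that is 132 per arm at the start.

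The sample size is correct and not in dispute.

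**2. Effect of leaving out balanced factors.** Let R² be the share of outcome variance explained by counselor, gender and cancer syndrome together. The article does not give it; 0.05 to 0.20 is assumed. Under good balance:

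- model SE without the factors (SD units): SE = √(2/n), which is 0.142 at n = 99 and 0.123 at n = 132
- true SE = SE × √(1 − R²)
- type I error, factors omitted = 2[1 − Φ(1.96/√(1 − R²))]
- power, factors omitted = Φ[(d/SE − 1.96)/√(1 − R²)]
- power, factors included = Φ[d/(SE√(1 − R²)) − 1.96]

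Worked case, R² = 0.20, n = 99: d/SE = 2.814 and √0.80 = 0.894. Type I error = 2[1 − Φ(2.191)] = 0.028. Power omitted = Φ(0.854/0.894) = 0.830. Power included = Φ(3.147 − 1.960) = 0.882.

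| R² | Model SE / true SE | Type I error, omitted | Power, 99 per arm: omitted / included | Power, 132 per arm: omitted / included |
|---|---|---|---|---|
| 0 | 1.00 | 0.050 | 0.804 / 0.804 | 0.901 / 0.901 |
| 0.05 | 1.03 | 0.044 | 0.810 / 0.823 | 0.907 / 0.915 |
| 0.10 | 1.05 | 0.039 | 0.816 / 0.843 | 0.913 / 0.929 |
| 0.20 | 1.12 | 0.028 | 0.830 / 0.882 | 0.925 / 0.953 |

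**3. Simulation check.** Minimization within counselor was simulated with 10 or 20 counselors, a 0.9 biased coin and 1,500 runs per setting (all assumed). With N = 198, 10 counselors and R² = 0.20, type I error was 0.037 omitted and 0.055 included; power was 0.817 and 0.881. At R² = 0.10, unadjusted power came out somewhat below the formula (0.778 with 10 counselors, 0.798 with 20), against 0.817 and 0.827 adjusted. Simulation standard error near 0.80 is about √(0.8 × 0.2/1500) = 0.010. The simulation supports the direction and rough size of the effect, not the third decimal.

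**4. Session duration (hypothesis 8).** Take 132 per arm, R² = 0.20 and a true increase of d = 0.3 (both assumed). d/SE = 0.3/0.1231 = 2.437. Power omitted = Φ[(2.437 − 1.960)/0.894] = 0.70; included = Φ(2.437/0.894 − 1.960) = 0.78. A real increase is missed about 30% of the time instead of 22%.

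**5. Chance entry of covariates.** Neither the number nor the level of the baseline tests is stated. For k independent tests at 5%, the chance that at least one flags is 1 − 0.95^k: 23% for 5, 34% for 8, 40% for 10. *Sociodemographic and clinical data* lists about ten candidate items, but gender is minimized and several items are related, so these figures are only indicative.

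**The case against.** The strongest reply is that the harm is modest and runs in the safe direction. That stands for the superiority hypotheses: type I error falls below 0.05, the effect estimate is not biased, and at d = 0.4 the formula keeps power at or above the planned 80%. A reader might infer inflated false positives because sessions share a counselor. The article does not support this, since counselors are balanced across arms, which narrows the true standard error. A reader might also credit adjustment with the whole rise from 0.80. That overstates the gain, because balance lifts unadjusted power too. The contrast at 99 per arm is 1 to 5 points over the assumed range, and 1 to 3 points at 132.

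A second reply is that a full covariate list is commonly left to the analysis plan, and that the bracketed prefix in the model's name leaves room for covariates. This is fair as to silence, and silence is not the point. The article states a selection rule, and for the primary outcomes it is the only route it gives for a covariate to enter.

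A third reply concerns what could be adjusted. It is tempting to say that the prevalence analysis should include the first PAHC score. The article does not support that. The baseline questionnaire returned before randomization holds worries, distress and demographics; the PAHC is completed later, shortly before the session, by counselees who are not blinded. It is a post-randomization measure, and adjusting for it could introduce bias. Nor can covariates simply be added to the awareness comparison, which applies Fisher's transformation to intraclass correlations.

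**Conclusion.** The point holds. The stated rule is a poor way to choose covariates, leaves the primary model unfixed, and in effect excludes the factors that the allocation was built around. If those factors explain 5-20% of outcome variance, the reported standard errors are about 3-12% too large, true type I error is 0.044-0.028, and power at d = 0.4 is 0.81-0.83 instead of 0.82-0.88 at 99 per arm (0.91-0.93 instead of 0.92-0.95 at 132). If they explain nothing, nothing is lost. The sizes rest on the assumed R², on good balance within counselor and on a roughly continuous outcome.

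This is not a finding that the trial is underpowered or its tests too liberal. The conservative direction is nevertheless not harmless throughout: for hypothesis 8, a standard error that is too wide makes the hoped-for absence of a significant increase easier to obtain.

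**What to change.** Delete the rule under *Comparability of intervention and control group* and present baseline characteristics descriptively by arm. In the analysis of (co)variance and logistic models, prespecify arm, counselor (random intercept, or fixed effects if counselors are few), gender and cancer syndrome. Keep the previous score as covariate for cancer worries and distress. Choose any further covariate in advance, on prognostic grounds. Do not adjust for the first PAHC, and leave the intraclass-correlation comparison outside this change.

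The cost is revised analysis wording and a few degrees of freedom. The minimization already requires counselor, gender and syndrome to be recorded, so no new data are needed.

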### Primary outcome measures

The primary outcomes of the trial are: (1) discussion of psychosocial problems; (2) counselors’ awareness of the counselees’ psychosocial problems; and (3) management of psychosocial problems during and after genetic counseling.

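### The rule to adjust for baseline differences cannot be carried out with the tests named for awareness, a primary outcome, and for satisfaction (hypothesis 5)

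*Protocol article*

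**What the plan says.** Under Comparability of intervention and control group, the protocol article first tests the arms against each other on sociodemographic and clinical characteristics: "Student’s t-test or appropriate non-parametric tests will be used". It then states that if "the groups are found to be statistically different on one or more baseline characteristics, these variables will be adjusted for in subsequent analyses". No outcome or analysis is exempted.

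Under Main research hypotheses, two of the three primary outcomes (issues discussed, and management) are assigned to analysis of (co)variance. Awareness, listed second under Primary outcome measures, is handled differently. An absolute-agreement intraclass correlation (ICC) is calculated "per domain for both the intervention and control group", and the two values are compared "using Fisher’s r-to-z transformation to test for statistical differences per domain".

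Under Secondary research hypotheses, satisfaction with the counseling process is compared between arms with Student's "t-tests and chi square tests, where appropriate". The other between-arm secondary analyses use analysis of (co)variance or logistic regression.

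**The concern.** The adjustment rule is general, but two of the named analyses have nowhere to put a covariate. If a baseline difference is found, two primary outcomes would be adjusted and the third would not, contrary to the rule. The analysts would then have to break the rule for awareness or pick a new awareness method after seeing the data. Either is an unplanned choice on a primary outcome. The same holds for hypothesis 5, at lower stakes because satisfaction is secondary.

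This is a conflict between two things the article does state, a rule and a set of tests. It is not a complaint that detail is absent.

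**Working it through.** **Each named test against the rule**

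| Outcome | Named method | Covariate term? |
|---|---|---|
| Issues discussed (primary) | Analysis of (co)variance | Yes |
| Awareness (primary) | Fisher z on two ICCs, per domain | No |
| Management (primary) | Analysis of (co)variance | Yes |
| Counselor initiation, time, duration | Analysis of (co)variance | Yes |
| Worries, distress | Analysis of covariance | Yes |
| Prevalence of specific problems | Logistic regression | Yes |
| Satisfaction (hypothesis 5) | t and chi-square tests | No |

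The Fisher statistic is [atanh(ICC₁) − atanh(ICC₂)] / √[1/(n₁−3) + 1/(n₂−3)]. Its only inputs are two coefficients and two sample sizes.

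**Sample size used below.** The plan's figure reproduces: for d = 0.4, two-sided alpha 0.05 (sidedness assumed) and power 0.80, 2(1.96 + 0.84)²/0.4² ≈ 98.1, so 99 per arm and 198 in total. Then 198/0.75 = 264 enrolled, or 132 per arm. This point does not dispute these figures.

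**How often the rule would be triggered.** The document fixes neither the list of variables nor the significance level. Assume k independent tests at 0.05:
- k = 5: 1 − 0.95⁵ = 23%
- k = 10: 1 − 0.95¹⁰ = 40%
- k = 15: 1 − 0.95¹⁵ = 54%

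The section on sociodemographic and clinical data supports about ten: age, gender, marital status, education, number of children, age of children, past service use, cancer history, age at diagnosis and known family mutation. Several of these are related to each other, and gender is balanced by minimization, so 40% is illustrative only.

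**What an unadjusted imbalance could do to a mean (satisfaction).** A baseline difference that just reaches significance is 1.96·√(2/99) = 0.28 SD at 99 per arm, or 1.96·√(2/132) = 0.24 SD at 132. With an assumed covariate-outcome correlation of 0.1 to 0.5, the unadjusted difference at 99 per arm shifts by 0.1 × 0.28 = 0.03 to 0.5 × 0.28 = 0.14 SD. The planning effect is 0.4.

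**What it could do to an ICC (awareness).** An ICC depends on the spread between people as well as on agreement. Assume an ICC of 0.40 and 25% more between-person variance in one arm. The ICC becomes 0.50/(0.50 + 0.60) = 0.45. On the z scale the change is 0.490 − 0.424 = 0.067, against a standard error of √(2/96) = 0.144, which is about 0.46 standard errors.

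**The case against.** The strongest reply is that the baseline rule works as an override. It comes first and is conditional, and the later sections give default methods. How each adjustment is carried out is the kind of detail an article leaves to the full protocol or analysis plan. Covariate-adjusted counterparts also exist: ICCs from a variance-components model with covariates, Fisher's z on partial correlations, and regression for satisfaction.

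Part of this stands. The limitation belongs to the tests as named, not to agreement or satisfaction in general. A reader might infer that awareness cannot be adjusted at all, and that would be wrong. But the article names no adjusted version. Moving from an absolute-agreement ICC to a partial correlation would also change what is measured, so the choice is not a mere detail.

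It also stands that the harm is limited. A reader might infer that the awareness result would be biased, or that about 40% of such trials would give a wrong awareness result. The documents support neither. Participants are randomized, so an unadjusted comparison is valid on average, and the 40% counts only how often the rule would be triggered under assumed independence.

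Nor does leaving out counselor breach the quoted rule, which covers only baseline characteristics found to differ. Counselor enters the recommendation for another reason: Recruitment and randomization balances the arms within each counselor.

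**Conclusion.** The conflict holds on the current text. As written, the adjustment rule cannot be applied to one of three primary outcomes or to hypothesis 5. It is an inconsistency in the plan, not a bias built into the trial, and it has no effect unless a baseline difference is observed.

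Where it does bite, the illustrations suggest a modest size: 0.03 to 0.14 SD for a mean at 99 per arm, and roughly half a standard error for an ICC. These rest on assumed correlations and variances that the document does not give. The conflict itself depends on none of them. It is worth correcting because a primary outcome is affected and the remedy needs no new data.

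**What to change.** - **Covariates.** Name a fixed set in advance, including the minimization factors (counselor, gender, cancer syndrome), and drop selection by baseline significance tests. Under randomization such differences arise by chance, and their significance does not measure prognostic value.
- **Satisfaction.** Use linear or logistic regression on arm plus these covariates.
- **Awareness.** Use a method that takes covariates and keeps absolute agreement. One option is a mixed model, per domain, of the absolute difference between counselor and counselee ratings on arm, covariates and counselor. The two ratings must first be put on a common scale, since the counselor gives one rating per domain and the counselee answers several items. Another option is arm-specific, covariate-adjusted ICCs from a variance-components model. The raw ICCs stay as description.

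The slope interaction (counselor rating on counselee rating, by arm) should not serve as the awareness effect, because it ignores systematic under-rating. Suppose control counselors rate everyone exactly one point too low and intervention counselors rate exactly right. Both slopes are 1 and the interaction is zero. With an assumed rating variance of 0.8, and a rater variance of 1²/2 = 0.5 in the control arm, the ICC is 0.8/(0.8 + 0.5) = 0.62 in control and 1 in intervention. The mean absolute difference, 1 against 0, also shows the gap.

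The cost is revised wording, slightly more modelling, and an awareness summary that readers know less well than an ICC. If the sponsor prefers the present tests, the minimum change is to state that awareness and satisfaction are exempt from the adjustment rule.
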